#### Studies I and II

In the previously mentioned intervention with ASSA, approximately 10 % of participants did not answer the self-report instruments after the intervention [32]. If we assume the same answering rate, 10 % more patients have to be included in each arm.

### Statistical analysis

#### Study I

The Wilcoxon signed rank test and the Kruskal–Wallis test will be used for changes in non-normally distributed variables (for psychological symptoms measured using the self-report instruments and for midnight salivary cortisol concentration).

#### Study II

The Kruskal–Wallis test will be used for changes in non-normally distributed variables (psychological symptoms and midnight salivary cortisol concentration).

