#### Randomization and allocation

The randomization and allocation of the coded patients will be performed by an independent statistician with the purpose of having as equal distribution as possible of sex and age in each intervention arm.

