##### Study II

Assessments will be performed for Groups 1, 2 and 3 at T0, T1 and T2; 1 year after T2 (T3) and at T4. For Groups 4 and 5, assessments will be performed at T0 and T4.

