### Self-report instruments

#### Studies I and II

The Hospital Anxiety and Depression Scale will be used at all measuring points to assess self-reported anxiety and depression [4, 5, 32, 37–39]. The cut-off level for each subscale recommended by the constructors of this scale (≥8 points) will be used for inclusion in the intervention [38]. In a study that compared the Swedish version of the Hospital Anxiety and Depression Scale with a structured clinical interview for DSM-III criteria, the optimal cut-off level for screening was ≥5 points for both subscales [39].

The 20-item Toronto Alexithymia Scale will be used at all measuring points to assess alexithymia [4, 19, 32, 37, 40–42]. This scale consists of 20 statements rated from 1 to 5, and is based on three subscales: ‘difficulty identifying feelings’ (seven statements), ‘difficulty describing feelings’ (five statements) and ‘externally oriented feelings’ (eight statements).The recommended cut-off level (≥61 points) will be used for inclusion in the intervention [41, 42].

The affinity dimension of the Structural Analysis of Social Behavior assessment tool will be used to assess self-image [23, 35, 43]. This test consists of 36 statements with response options on a scale between 0 and 100; the results are summarized into eight clusters. High scores for the clusters ‘blaming self’, ‘hating self’ and ‘ignoring self’; and low scores for the clusters ‘accepting self’, ‘loving self’ and ‘nourishing self’ form a negative self-image. A negative self-image is defined as results below 284 points. The Structural Analysis of Social Behavior test will be used at T0 and at T4.

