### Primary and secondary outcome measures

In both studies, the primary outcome measure is the change in depression symptoms. Secondary outcome measures are changes in alexithymia and anxiety symptoms and self-image measures; changes in HbA1c concentration and midnight salivary cortisol concentration; use of antidepressants, and incidence of diabetes complications and mortality.

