### Power calculations for sample size

The standard deviation was 2.8 for the individual changes of Hospital Anxiety and Depression Scale – depression subscale after our intervention with ASSA for patients with chronic benign pain (calculated from raw data) [32].

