#### Studies I and II

A paired-samples *t* test will be used for continuous and normally distributed variables (HbA1c concentration). The associations between outcome variables and baseline characteristics will be modelled using linear regression analysis (HbA1c concentration, midnight salivary cortisol concentration, psychological symptoms); logistic regression analysis will be used for categorical outcomes (incidence of diabetes complications and use of antidepressants).

Cox proportional-hazards regression will be used to analyze effects on mortality. Missing values of the self-report instruments will be imputed using multinomial logistic regression on the other variables in the same subgroup [53]. Imputation will be performed for the depression and anxiety subscales of the Hospital Anxiety and Depression Scale if there are at most two missing items for each subscale; for the 20-item Toronto Alexithymia Scale if there is at most one missing item for each subscale (‘difficulty identifying feelings’, ‘difficulty describing feelings’ and ‘externally oriented feelings’) and for the Structural Analysis of Social Behavior tool if there is at most one missing item for each of the eight clusters. Statistical significance will be considered for *P* < 0.05.

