## Discussion

Diabetes is a progressive and demanding chronic disease, which requires emotional adaptation [1]. Previous research has shown that alexithymia is a risk factor for depression [15], which is deleterious for patients with diabetes [4–7]. Also, a deficit in the awareness of affects results in abnormal physiological reactions and impaired capacity for self-care [13]. An advanced capacity for self-care is necessary in diabetes.

For this reason, we were interested in finding interventions focusing on increased emotional awareness and verbal expressiveness. We have chosen to test the ASSA [30, 32, 37] against BBAT [34–36] in two studies. In Study I, we perform a two-arm randomized controlled trial with patients with type 1 or type 2 diabetes from one hospital diabetes outpatient clinic. In Study II, ASSA, BBAT and ‘treatment as usual’ will be compared in a three-arm randomized controlled trial for patients with type 2 diabetes from primary care units.

We expect the ASSA method to be more efficient than BBAT in reducing depressive symptoms. In the ASSA intervention, patients are systematically trained to identify and describe feelings, and are also presented with advanced affect theory. In BBAT, patients focus more on bodily features, such as breathing, grounding, stability, centring, flexibility and flow [36]. The patients undergoing BBAT are not systematically trained to identify and describe feelings but they are encouraged to observe and accept sensations and emotions that awaken during the treatment sessions [36]. As neither of the two interventions is ‘placebo’, we think it is important to compare both ASSA and BBAT with treatment as usual.

We have chosen reduction of depression symptoms as the primary outcome measure, even though some patients were not depressed at the time of inclusion. A reduction in depression symptoms might be of value even for patients not fulfilling our criteria for self-reported depression. A lower cut-off level (≥5 points) has been proposed for the depression subscale of the Swedish version of Hospital Anxiety and Depression Scale than we have chosen to use. This means that the sensitivity for depression might be less than optimal in our study [39].

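### Study II: the unadjusted Kruskal–Wallis test on depression change is valid, but less efficient than a comparison adjusted for the baseline score already collected

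*Protocol article*

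**What the plan says.** All references are to the protocol article.

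- **Outcome** (Primary and secondary outcome measures): "In both studies, the primary outcome measure is the change in depression symptoms".
- **Test** (Statistical analysis, Study II): the Kruskal–Wallis "test will be used for changes in non-normally distributed variables (psychological symptoms and midnight salivary cortisol concentration"). No covariate is named. Study I names the same test alongside the Wilcoxon signed rank test.
- **Regression** (Statistical analysis, Studies I and II): "The associations between outcome variables and baseline characteristics will be modelled using linear regression analysis". Psychological symptoms are among the outcomes listed, but no term for randomised arm is stated.
- **Baseline score** (Self-report instruments): "The Hospital Anxiety and Depression Scale will be used at all measuring points to assess self-reported anxiety and depression". The Study II schedule reads: "Assessments will be performed for Groups 1, 2 and 3 at T0, T1 and T2; 1 year after T2 (T3) and at T4".
- **Allocation** (Randomization and allocation): carried out by an independent statistician "with the purpose of having as equal distribution as possible of sex and age in each intervention arm".
- **Population** (Discussion): depression was chosen as primary outcome "even though some patients were not depressed at the time of inclusion".
- **Sample size** (Power calculations): "The standard deviation was 2.8 for the individual changes of Hospital Anxiety and Depression Scale" (depression subscale). The target is a 1.4-point difference in one of three arms. ANOVA requires 60 per arm, raised by 15 % to 70 for Kruskal–Wallis.

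**The concern.** A change score subtracts the whole baseline value, whatever the actual baseline–follow-up relation. When that relation is weaker than one-to-one, change stays correlated with baseline: high scorers tend to fall back and low scorers have little room to fall. Patients can qualify through depression, anxiety, alexithymia or negative self-image, so baseline depression will be heterogeneous and this unexplained variation will not be small. A chance baseline imbalance between arms also feeds into the comparison.

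At stake is precision in a trial whose authors foresee recruitment difficulties. The choice is open to comment because the article names the test and sizes Study II for it; it is not a detail left to a later document. The regression paragraph does not supply the missing adjustment, since it describes associations with baseline characteristics and not an adjusted comparison of arms.

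**Working it through.** **Inputs.** From the protocol: SD of change 2.8, difference 1.4, significance level 0.05, three equal arms, 60 per arm (ANOVA) and 70 (Kruskal–Wallis). Not given, so assumed: the baseline–follow-up correlation ρ, shown for 0.5–0.8, and the shape of the score distribution.

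**1. Reproduce the plan's figures.** The noncentrality is λ = n Σ(μᵢ − μ̄)²/σ². With means 0, 0 and 1.4, Σ(μᵢ − μ̄)² = 1.307, and 1.307/2.8² = 1/6, so λ = n/6. At n = 60, λ = 10 and power is 80.8 % (59 per arm gives 80.1 %). Then 60 × 1.15 = 69, in line with the stated 70. The sample size is sound on its own terms.

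**2. Why baseline adjustment helps.** With baseline SD σ₀ and follow-up SD σ₁:

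Var(change) − Var(follow-up given baseline) = (σ₀² + σ₁² − 2ρσ₀σ₁) − σ₁²(1 − ρ²) = (σ₀ − ρσ₁)² ≥ 0.

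With equal SDs the variance ratio is (1 + ρ)/2: 0.75 at ρ = 0.5 and 0.90 at ρ = 0.8. The gain shrinks as ρ approaches 1.

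**3. Analytic power of a linear adjusted model (ANCOVA).** Residual SD = 2.8 × √((1 + ρ)/2), noncentral F, one degree of freedom spent on baseline.

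| ρ | Residual SD | Power at 70 per arm | n per arm for 80 % |
|---|---|---|---|
| 0.5 | 2.425 | 94.9 % | 45 |
| 0.6 | 2.504 | 93.4 % | 48 |
| 0.7 | 2.581 | 91.9 % | 51 |
| 0.8 | 2.656 | 90.3 % | 54 |

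Spending three degrees of freedom (for example on baseline, sex and age) leaves these sample sizes unchanged.

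**4. Comparison with the planned test itself.** The right comparator is Kruskal–Wallis at 70 per arm, not a t test or ANOVA. Simulated power, 2,000 trials per setting; bounded scores are rounded to 0–21 with an assumed mean of 6.

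| ρ | Normal: Kruskal–Wallis | Normal: ANCOVA | Bounded: Kruskal–Wallis | Bounded: ANCOVA |
|---|---|---|---|---|
| 0.5 | 84.2 % | 94.3 % | 83.2 % | 94.2 % |
| 0.6 | 85.5 % | 93.9 % | 83.1 % | 92.3 % |
| 0.7 | 85.3 % | 91.5 % | 80.9 % | 90.0 % |
| 0.8 | 84.7 % | 90.3 % | 79.6 % | 87.2 % |

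ANCOVA's type I error with bounded scores was 4.7–5.4 %. A separate simulation over the same ρ range gave 79–85 % for Kruskal–Wallis and 88–96 % for ANCOVA.

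**5. Skewed scores.** The protocol expects non-normality, so this case matters. With gamma-shaped scores (assumed mean 5), rounded and bounded to 0–21, Kruskal–Wallis against linear ANCOVA gave 88 % v 92 % at ρ = 0.5, 89 % v 87 % at 0.7 and 88 % v 83 % at 0.8. Another skewed, bounded simulation gave 88 % v 87 % and 92 % v 89 % over ρ = 0.7–0.8. The linear model's advantage is therefore gone by about ρ = 0.7.

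A rank-based analysis adjusted for baseline reached 86–97 % across the normal, bounded and skewed settings, with type I error near 5 %. Its margin is clear with skewed scores but can be very small with near-normal scores at high ρ.

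**The case against.** The strongest reply is that this is a choice between two valid analyses, and that the rank test was chosen because the scores are expected to be non-normal. Part of this stands. Besides the skewed results above, with a heavy-tailed follow-up residual (t, 3 df, assumed) Kruskal–Wallis reached 97–98 % against 90–92 % for linear ANCOVA at ρ = 0.7–0.9. A reader might infer that a linear adjusted model always gives more power at no cost; it does not. What survives is the case for using baseline in a form that tolerates non-normality. The rank-adjusted analysis was not run in the heavy-tailed setting.

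Other inferences go beyond the documents:

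- **Study II is underpowered or its test wrong.** Kruskal–Wallis at 70 per arm attains about 80 % or more, and the 15 % allowance does its job.
- **No estimate or confidence interval will be reported.** The article only names tests and commits the report to CONSORT. Silence in a condensed article is not a decision to withhold estimates.
- **Ignoring sex and age loses a known amount of precision.** Nothing allows that to be quantified. All the computed gain comes from baseline depression; including sex and age rests only on their role in allocation.
- **The comparison belongs at T2.** The Abstract sizes both studies at the last follow-up session. The argument for adjustment holds at any visit and does not choose one.
- **Study I can be changed freely.** Its T2 assessments had already been performed in an open-label study, so replacing its primary analysis would be post hoc. At 21 per arm the t-test gain would be from 35 % to about 40–45 % (ρ = 0.7 to 0.5), which does not rescue it.

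The calculations also ignore the instructor and group clustering that the protocol describes.

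**Conclusion.** The point holds for Study II as a matter of efficiency. The planned test is valid and adequately sized, but it leaves unused information that the trial already collects. At 70 per arm and assumed ρ of 0.5–0.8, power rises from about 79–85 % to about 88–96 % with near-normal or bounded scores (lowest single setting 87 %). With skewed scores the linear model can tie or lose from ρ = 0.7 upward, while the rank-adjusted version keeps the gain.

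These sizes rest on a change SD of 2.8, a 1.4-point shift in one arm, independent patients, and assumed correlations and score shapes. That conditional variance never exceeds change-score variance needs no such assumption, but it does not by itself guarantee more power than a rank test. This is a recommended improvement, not a correction of an error.

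**What to change.** **Study II, before recruitment starts.** Make the primary comparison a model of follow-up depression score on randomised arm, with T0 depression score, sex and age as covariates, at the visit the protocol designates as primary. Report adjusted differences between arms with 95 % confidence intervals. Because non-normal scores are expected, specify in advance either robust standard errors for a linear model or a baseline-adjusted rank or proportional-odds model; the skewed simulations favour a rank-based form. Keep Kruskal–Wallis on change as a sensitivity analysis.

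**Study I.** Leave the stated primary analysis in place and add the adjusted analysis only as a dated supplementary one.

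**Cost.** No extra patients or data for Study II. The price is added model assumptions and, for the linear model, a move from comparing ranks to comparing means. Robust standard errors protect the linear model's inference but do not restore power lost to skewness.

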#### Studies I and II

A paired-samples *t* test will be used for continuous and normally distributed variables (HbA1c concentration). The associations between outcome variables and baseline characteristics will be modelled using linear regression analysis (HbA1c concentration, midnight salivary cortisol concentration, psychological symptoms); logistic regression analysis will be used for categorical outcomes (incidence of diabetes complications and use of antidepressants).

Cox proportional-hazards regression will be used to analyze effects on mortality. Missing values of the self-report instruments will be imputed using multinomial logistic regression on the other variables in the same subgroup [53]. Imputation will be performed for the depression and anxiety subscales of the Hospital Anxiety and Depression Scale if there are at most two missing items for each subscale; for the 20-item Toronto Alexithymia Scale if there is at most one missing item for each subscale (‘difficulty identifying feelings’, ‘difficulty describing feelings’ and ‘externally oriented feelings’) and for the Structural Analysis of Social Behavior tool if there is at most one missing item for each of the eight clusters. Statistical significance will be considered for *P* < 0.05.

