**Methods:**

Two studies will be performed. Study I is an open-labeled parallel-group study with a two-arm randomized controlled trial design. Patients are randomized to either affect school with script analysis or to basic body awareness treatment. According to power calculations, 64 persons are required in each intervention arm at the last follow-up session. Patients with type 1 or type 2 diabetes were recruited from one hospital diabetes outpatient clinic in 2009. The trial will be completed in 2016. Study II is a multicentre open-labeled parallel-group three-arm randomized controlled trial. Patients will be randomized to affect school with script analysis, to basic body awareness treatment, or to treatment as usual. Power calculations show that 70 persons are required in each arm at the last follow-up session. Patients with type 2 diabetes will be recruited from primary care. This study will start in 2016 and finish in 2023. For both studies, the inclusion criteria are: HbA1c concentration ≥62.5 mmol/mol; depression, alexithymia, anxiety or a negative self-image; age 18–59 years; and diabetes duration ≥1 year. The exclusion criteria are pregnancy, severe comorbidities, cognitive deficiencies or inadequate Swedish. Depression, anxiety, alexithymia and self-image are assessed using self-report instruments. HbA1c concentration, midnight salivary cortisol concentration, blood pressure, serum lipid concentrations and anthropometrics are measured. Data are collected from computerized medical records and the Swedish national diabetes and causes of death registers.

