#### Intervention criteria

For both studies, these are either a HbA1c concentration of at least 62.5 mmol/mol or at least one of: self-reported depression, anxiety, alexithymia or a negative self-image (Fig. 1).

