### Measurements

#### Study I and II

According to the Swedish national guidelines for diabetes management in 2009, the recommended goal for treatment was for HbA1c concentrations of less than 52 mmol/mol. However, since goals should be individualized, a higher cut-off value was chosen in this study: venous HbA1c concentration (IFCC units) ≥62.5 mmol/mol, (Mono-S ≥7 %, NGSP ≥7.87 %) [44]. Analyses will be performed with high pressure liquid chromatography, (HPLC - variant II, Turbo analyzer, Bio-Rad®, Hercules, CA, USA) [45].

Serum lipids will be analyzed using the enzymatic colour test (Olympus AU®, Tokyo, Japan). Blood lipids and HbA1c will be analyzed at the Department of Clinical Chemistry, Växjö Central Hospital.

Blood pressure, waist circumference, weight and length will be measured by a nurse, according to standard procedures. Abdominal obesity is defined for men as waist circumference ≥1.02 m. and for women as waist circumference ≥0.88 m [4, 5]. General obesity is defined as body mass index ≥30 kg/m^2^ for both sexes [4].

Midnight salivary samples will be collected between 23.30 and 00.30 hours using a Salivette sampling device [5, 46–49] (Salivette®, Sarstedt, Nümbrecht, Germany). Assays will be performed at the Department of Clinical Chemistry, Lund University Hospital, Lund, using Roche Cobas Cortisolassay®, a competitive electrochemiluminescence immunoassay [5, 46–49], using an Elecsys 2010 immunoanalyzer system (Roche Diagnostics, Mannheim, Germany). Patients will receive written and oral instructions before sampling [5].

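### In both studies HbA1c change is assigned a within-patient paired t test, and no comparison of HbA1c between the randomised arms is stated

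*Protocol article*

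**What the plan says.** Under Primary and secondary outcome measures, the Protocol article lists "changes in HbA1c concentration and midnight salivary cortisol concentration" among the secondary outcomes of both studies. The stated aims are comparisons between arms: ASSA with BBAT in Study I, and both with treatment as usual in Study II (Objective and research questions).

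Statistical analysis gives HbA1c, for both studies, a paired-samples t test: "test will be used for continuous and normally distributed variables (HbA1c concentration"). The next sentence adds a regression: "The associations between outcome variables and baseline characteristics will be modelled using linear regression analysis". HbA1c is among its outcomes; randomised arm is not mentioned.

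The Kruskal–Wallis test, which does compare groups, is kept for other variables. In Study I it is named together with the Wilcoxon signed rank test "for psychological symptoms measured using the self-report instruments and for midnight salivary cortisol concentration". In Study II the Kruskal–Wallis "test will be used for changes in non-normally distributed variables (psychological symptoms and midnight salivary cortisol concentration").

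On selection, the Abstract states "For both studies, the inclusion criteria are: HbA1c concentration ≥62.5 mmol/mol" and adds a psychological criterion. Intervention criteria words it differently: "these are either a HbA1c concentration of at least 62.5 mmol/mol or at least one of" four psychological criteria. Measurements explains the threshold: "a higher cut-off value was chosen in this study: venous HbA1c concentration (IFCC units").

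HbA1c is measured at baseline (T0), again before the intervention (T1), after it (T2), one year later in Study II only (T3), and at T4. The analysis section does not say which two visits the paired test uses.

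**The concern.** A paired t test asks whether the mean within a set of patients has moved. HbA1c can move without any effect of ASSA or BBAT. Diabetes and other treatment is unrestricted (Treatment as usual), follow-up runs for years, and patients chosen for a high value tend to have a lower one next time. Randomisation lets these influences be subtracted, but only if the arms are compared.

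Followed as written, the plan could report a significant HbA1c fall after ASSA, BBAT or both without estimating a treatment effect. In Study II the usual-care arm, which the Discussion considers important because neither intervention is a placebo, would play no part in the HbA1c result. Setting one arm's p-value beside another's does not repair this. If two arms change equally and each within-arm test has 50 % power, exactly one is significant with probability 2 × 0.5 × 0.5 = 0.5.

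**Working it through.** **1. The plan's own figures.** No figure is given for HbA1c. The group sizes used below come from Power calculations for sample size, which concerns the depression subscale, and they reproduce. With SD 2.8 and difference 1.4, n = 2 × (1.96 + 0.84)² × (2.8/1.4)² ≈ 63 per arm by the normal approximation, and 63.8, so 64, by the t test. Power at 21 per arm is 0.367 (stated: 37 %). In Study II, 60 per arm gives ANOVA power 0.808, and 60 × 1.15 = 69 against the stated 70. These figures do not bear on the HbA1c analysis beyond supplying n = 21 and n = 70.

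**2. Which outcomes have a between-arm test?**

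| Outcome | Named analysis | Compares arms? |
|---|---|---|
| Psychological scores, cortisol (Study I) | Wilcoxon signed rank and Kruskal–Wallis | Yes, by Kruskal–Wallis |
| Psychological scores, cortisol (Study II) | Kruskal–Wallis | Yes |
| HbA1c (both studies) | Paired t test; regression on baseline characteristics | Not as stated |

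**3. Expected fall with no treatment effect.** Assumptions, none of them in the article: clinic mean μ = 60 or 65 mmol/mol, SD 13, correlation r = 0.7, 0.8 or 0.9 between any two visits. Every patient is selected on T0 HbA1c ≥ 62.5, and T0 is the pre-value.

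Fall = (1 − r) × SD × φ(a)/(1 − Φ(a)), with a = (62.5 − μ)/SD.

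- μ = 60: a = 2.5/13 = 0.192, φ/(1 − Φ) = 0.3916/0.4238 = 0.924. At r = 0.7 the fall is 0.3 × 13 × 0.924 = 3.6.
- μ = 65: a = −0.192, φ/(1 − Φ) = 0.3916/0.5762 = 0.680. At r = 0.9 the fall is 0.1 × 13 × 0.680 = 0.9.

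**4. Chance of a significant fall within one arm** (2,000 simulated trials per row and group size, no treatment effect, two-sided 5 % test, so 2.5 % nominal in this direction):

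| μ | r | Fall (mmol/mol) | n = 21 | n = 70 |
|---|---|---|---|---|
| 60 | 0.7 | 3.6 | 36 % | 89 % |
| 60 | 0.8 | 2.4 | 25 % | 70 % |
| 60 | 0.9 | 1.2 | 16 % | 41 % |
| 65 | 0.7 | 2.7 | 23 % | 62 % |
| 65 | 0.8 | 1.8 | 17 % | 44 % |
| 65 | 0.9 | 0.9 | 10 % | 25 % |

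**5. The two conditions relaxed.**

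- *T1 as pre-value.* The paired test rejects in about 4–6 % of runs (two-sided), the nominal level. Selection at T0 no longer drives a fall in this model.
- *Either/or selection.* Suppose a fraction q of patients meets a psychological criterion independently of HbA1c, with q = 0.3–0.5 (assumed). With s = 1 − Φ(a), the fall becomes (1 − r) × SD × φ(a) × (1 − q)/(s + q(1 − s)). For μ = 60, r = 0.7, q = 0.3: 0.3 × 13 × 0.3916 × 0.7/(0.4238 + 0.3 × 0.5762) = 1.8. For q = 0.5 it is 1.1. A simulation of 6,000 trials gives a false significant fall in 6–12 % at n = 21 and 14–32 % at n = 70.

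**6. Comparing the arms.** In the runs of step 4, with strict selection and T0 as pre-value, a two-sample t test of change between two arms rejects in 4.5–5.5 %, the nominal 5 %.

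**The case against.** The strongest reply is that a journal article condenses the plan, and that the regression may well include arm. Condensation can explain something left out. Here, however, a specific test is named for HbA1c and it answers a different question from the stated aim. The regression is described by baseline characteristics, and randomised arm is not one.

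Four stronger readings are tempting, and the article does not support them.

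- *Regression to the mean will produce apparent benefit.* It can, but only if T0 is the pre-value and selection on HbA1c is strict. The paired visits are not named, and the Abstract and Intervention criteria conflict on whether high HbA1c is required. More extreme assumptions (mean down to 55, SD up to 15, correlation down to 0.6) bring the false-positive chance as high as 74 % at 21 per arm and above 99 % at 70. Nothing in the article supports that corner of the range.
- *The primary outcome also lacks a between-arm test, because Study I lists the signed rank test.* The same sentence names Kruskal–Wallis, and Study II names it too.
- *Depression scores are subject to the same selection.* A depression score of at least 8 is one of several routes to eligibility and is not required. The Discussion says that some patients were not depressed at inclusion.
- *The logistic models also omit arm.* Their predictors are simply not listed, which an article may leave to the full plan.

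A simple between-arm test of change would also hold its error rate (step 6). Preferring ANCOVA is therefore a matter of precision and of handling baseline imbalance, not of validity.

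**Conclusion.** The point stands for HbA1c in both studies: a within-patient test is named, no between-arm comparison is stated, and the aims need one. This conclusion rests on the text alone and requires no assumption about HbA1c values.

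The size of the possible error does rest on assumptions. With mean 60–65, SD 13, correlation 0.7–0.9, strict selection and T0 as pre-value, the spurious fall is 0.9–3.6 mmol/mol, and a false significant fall occurs in about 10–36 % of cases at 21 per arm and 25–89 % at 70 per arm. Either/or selection dilutes this, and a T1 pre-value largely removes it. Even then, time trends and concurrent treatment remain mixed with the effect of the intervention.

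This should be fixed, but it does not threaten the main conclusion. One secondary outcome is affected, and the primary outcome has a between-arm test in both studies.

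**What to change.** - Make a between-arm ANCOVA the HbA1c effect analysis in both studies: follow-up HbA1c on randomised arm, adjusted for pre-intervention HbA1c and for sex and age, the two factors that the allocation is meant to balance.
- Name the pre-value visit (T0 or T1) and the follow-up visit or visits (T2, T3 in Study II, T4).
- Report adjusted differences with 95 % confidence intervals: ASSA versus BBAT in Study I; ASSA versus usual care, BBAT versus usual care and ASSA versus BBAT in Study II.
- Keep the paired t test as a description of change within arms only.
- Reconcile the HbA1c criterion in the Abstract with that in Intervention criteria, so that readers know how patients were selected.

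The cost is wording. The HbA1c measurements are already scheduled. For Study II the text can be settled before recruitment starts. For Study I, where data up to T2 have been collected, the change should be dated and reported as made at that stage.
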